#### Process Evaluation

This is a central component of the evaluation of this translational study in order to assess whether the program is implemented as planned, achieves population reach and whether it is feasible in the primary care field setting. Details of the process evaluation components are shown in Table 1.

**Table 1 T1:** Process evaluation components in the Sydney Diabetes Prevention Program

Evaluation Component	Data source and format	Timeframe
Screening, participation and recruitment rates	Administrative documentation from Divisions of General Practice	Ongoing during recruitment
Program fidelity, program completion, intervention completed	Participants' database	Ongoing
Assessment of practice staff awareness and engagement with program	Telephone administered questionnaires to selected doctors and practice staff	Ongoing
Barriers to recruitment, and program delivery	In-depth-interviews and focus groups with practice staff	Ongoing
Challenges in program delivery and patient maintenance in program.	Focus group with lifestyle officers	Ongoing
Participants' barriers to attendance at group sessions	From participants via the Lifestyle Officers	Three months after group sessions completed
Number and type of organisations participating, perceived level of collaboration, barriers and success factors for community-based programs/services for physical activity and weight management	In-depth-interviews and focus groups with key stakeholders	Towards the end of the Program, when 12 month follow up data available

#### Economic Evaluation

The economic evaluation will adopt a health system perspective by measuring costs at Area Health Service, Government and general practice levels. It will also use a limited societal perspective by measuring direct costs to participants. In addition, the estimated costs of a state-wide rollout of the SDPP will be reported. The base cost year will be 2008. No discounting will be applied as this is a 12-month program including intervention and follow-up.

The economic evaluation will compare the cost of program implementation with its intermediate outcomes. The results of the study will be used to build a model of future costs and effects beyond the study period using Australian population and risk factor data [28-32]. Information to be collected about resource use will include program expenses (e.g. cost of screening and delivering the intervention), individual level and health system expenditure data. These will include direct health-related costs (visits to health professionals, hospitalisation, medication use etc) and direct non-health costs (gym subscription, exercise equipment, etc.) relevant to diabetes prevention, and indirect costs (e.g. sick days). This information will allow estimation of the cost per estimated case of diabetes prevented and cost per outcome (e.g. cost per kg weight loss; cost per change in additional time of physical activity, etc). Modelling will project these calculations beyond the study period using lives saved, life-years saved and quality-adjusted life-years (QALYs) gained to calculate the benefits associated with this program.

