#### Impact Evaluation

Outcomes are assessed at baseline and 12 months by research staff, using a combination of in-person assessment and CATI questionnaires. Physical activity is assessed using the Physical Activity Scale for the Elderly (PASE), which has established reliability and validity [26]. Dietary intake (including total fat, saturated fat and fibre) is assessed by a self-completed 3-day non-weighed food record, which is analysed using Foodworks [27].

Weight, height, waist circumference and blood pressure are measured using standard methods. Blood is collected for measurement of fasting plasma glucose and lipids. Additional questions on socio-demographic characteristics, concomitant diseases and medications, smoking, alcohol, social support, self-efficacy for lifestyle change, and quality of life are asked at the baseline and 12 month CATI surveys.

Analyses of these data will determine whether the program goals are achieved by individuals, by the group as a whole and differentially by sub-groups (e.g. GP Division and gender). In addition, these data will be used to model the projected impact of the program beyond the 12-month intervention period.

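### The no-discounting rule rests on the 12-month programme, but the same section projects costs, life-years and QALYs beyond it; applied to the model, the rule would understate cost per QALY

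*Protocol article*

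**What the plan says.** All the relevant text is in the Protocol article, mainly under Economic Evaluation.

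- **The rule.** The first paragraph sets the perspectives, mentions the cost of a state-wide rollout, fixes the price year ("The base cost year will be 2008") and ends with "No discounting will be applied as this is a 12-month program including intervention and follow-up". The length of the programme is the only reason given.
- **The model.** The second paragraph starts from a comparison of implementation cost with intermediate outcomes, then adds: "The results of the study will be used to build a model of future costs and effects beyond the study period". It closes with "Modelling will project these calculations beyond the study period using lives saved, life-years saved and quality-adjusted life-years (QALYs) gained".
- **When programme costs arise.** The resources to be costed include "program expenses (e.g. cost of screening and delivering the intervention", which belong to the programme itself.
- **A second mention of projection.** Under Impact Evaluation, "these data will be used to model the projected impact of the program beyond the 12-month intervention period".

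No discount rate, model horizon or model cost stream appears anywhere in the article. The 2008 base year sets the price level and says nothing about time preference.

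**The concern.** Discounting is unnecessary when costs and effects all fall within about a year. That is the only situation the stated reason covers. Once costs and QALYs are projected for years after the programme, their timing matters: the programme is paid for at the start, while the survival and quality-of-life gains from avoiding or delaying diabetes come later. An analyst who takes the unqualified sentence at its word would leave the model undiscounted and count a QALY many years away the same as one gained now.

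What is at stake is the modelled cost per QALY and cost per life-year. Cost-effectiveness is listed among the additional aims at the end of the Background, and the article presents the study as relevant to policy. An understatement that favours the programme would therefore reach the readers for whom the economic results are intended.

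**Working it through.** **No figure to reproduce.** The article states no cost per QALY, rate or horizon. The check is a comparison of the text with itself, followed by an illustration of size.

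**Step 1: does the reason cover the outputs?**
- Costs and outcomes measured over 12 months, and ratios such as cost per kg lost: yes.
- Future costs, lives saved, life-years and QALYs after the study: no. By the article's own words these lie outside the period that the reason refers to.
- Text limiting the rule to the first group, or giving a rate for the second: none.

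**Step 2: size under assumptions.** From the document: programme cost arises within the programme, benefits are projected beyond it, and the stated rule is a rate of 0%. Assumed: annual rate r of 3% or 5%; QALYs gained equally in each of years 1 to T; programme cost in the first year, left undiscounted; no other costs.

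Cost per QALY, discounted relative to undiscounted = T / A, where A = Σ (1+r)^−t for t = 1 to T = [1 − (1+r)^−T] / r.

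| Horizon T | A at 3% | Factor at 3% | A at 5% | Factor at 5% |
|---|---|---|---|---|
| 5 years | 4.580 | 5/4.580 = 1.09 | 4.329 | 5/4.329 = 1.15 |
| 10 years | 8.530 | 10/8.530 = 1.17 | 7.722 | 10/7.722 = 1.30 |
| 20 years | 14.877 | 20/14.877 = 1.34 | 12.462 | 20/12.462 = 1.60 |
| 30 years | 19.600 | 30/19.600 = 1.53 | 15.372 | 30/15.372 = 1.95 |

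**Step 3: benefits that start late.** If gains begin only after L years, the factor is (T − L) / Σ (1+r)^−t for t = L+1 to T. For T = 20 and L = 5 it is 15/10.298 = 1.46 at 3% and 15/8.133 = 1.84 at 5%. For T = 30 and L = 10 it is 20/11.070 = 1.81 and 20/7.651 = 2.61.

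**Step 4: future costs or savings.** Set programme cost to 1, T = 20 and L = 5, and let the extra costs or savings fall in the same years as the QALYs.
- Savings of 0.02 a year. Undiscounted: (1 − 0.02×15)/15 = 0.0467. Discounted: (1 − 0.02×10.298)/10.298 = 0.0771 at 3%, and 0.1030 at 5%. Factors: 1.65 and 2.21, so the gap widens.
- Added costs of 0.10 a year. Undiscounted: (1 + 0.10×15)/15 = 0.1667. Discounted: 0.1971 at 3% and 0.2230 at 5%. Factors: 1.18 and 1.34, so the gap narrows but keeps its direction.
- Added costs falling later than the benefits (QALYs in years 1 to 20, costs in years 15 to 30). At 0.05 a year the factors are 1.06 and 1.14. At 0.20 a year they are 0.85 and 0.80, and at 0.50 a year 0.77 and 0.67. Here the direction reverses. The article describes no such pattern.

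**The case against.** The strongest reply is that the sentence carries its own limit. A reason that appeals to a 12-month programme can only concern 12-month quantities, and the sentence closes the paragraph on measured costs, perspectives and price year. The model comes in the next paragraph as a further step. On that reading the within-study results are rightly undiscounted, and the model's rate is simply not given, as is usual for a condensed article.

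Much of this stands. The authors may well have meant only the within-study analysis. A missing model rate or horizon would not by itself be a fault of a journal article. A reader might infer that the plan has decided to leave QALYs undiscounted and that the published ratio will therefore be too favourable. The text does not support that: it is ambiguous, and the outcome depends on how the rule is applied. Nor does the article treat cost per QALY as its headline result. It ties the rollout to estimated costs, and it makes policy recommendations conditional on the programme being shown effective.

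What does not stand is the claim that nothing needs correcting. The article is not silent on discounting. It states an unqualified rule under the heading that also contains the model, on a ground that fails for part of that section, and an analyst following it literally would get a wrong result.

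**Conclusion.** The point holds in conditional form. The stated reason does not extend to the projected results, and if the rule is applied to them, cost per QALY and cost per life-year would be understated. The direction follows from early programme costs and later benefits; only large added costs falling after the benefits reversed it in the checks.

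The size cannot be derived from the article. Under the assumptions shown, it runs from about 9% to 15% for a 5-year model to roughly 1.5 to 2 times for a 30-year one. It would be larger if benefits start late or bring savings, and smaller if they bring added costs. It would be wrong to quote only the long-horizon factors, because the model could be short.

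Severity is moderate. The issue affects modelled outputs under an additional aim. The primary outcomes in the Statistical methods section, the data collection and the 12-month cost-per-outcome ratios are untouched.

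**What to change.** State that no discounting applies to within-study (12-month) costs and cost-per-outcome ratios only. For every result projected beyond 12 months, discount both costs and health effects at one annual rate fixed before the model is run, with sensitivity analyses that include 0%. This covers cost per case of diabetes prevented if the cases are counted after month 12. The article gives no basis for a particular rate, so the sponsor should choose one and state its source.

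The cost is a sentence or two in the economic plan and one parameter in the model, with no change to design or data collection. The downside for the sponsor is that the modelled cost per QALY is likely to look less favourable than an undiscounted one. The 0% sensitivity analysis keeps the undiscounted figure visible.

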#### Statistical methods

Analysis at 12 months will determine the extent that program goals were achieved, through overall and sub-group analysis. Primary outcomes which will be reported include weight loss (and 5% weight loss goal achievement), physical activity levels (in minutes per week of overall intentional activity, and sessions per week of strength training) and PASE scores, dietary measures (total energy/day, estimated fibre intake (gm/1,000 kcal), total fat intake (gm/day), fat as a proportion of total energy intake and saturated fat as a proportion of daily energy intake), and proportions of the cohort achieving 1,2,3,4, or all 5 goals. Logistic regression analysis will be used to examine factors associated with the achievement of program goals. Separate models will examine predictors of 5% weight loss, achievement of 210 min/day of physical activity, and achievement of dietary goals.

Missing data due to either refusal to respond to selected questions or withdrawal from the program before the endpoint will be dealt with by imputing values for the discrepant self-reports using data from "similar" participants or using last observation carried forward (LOCF) techniques when appropriate.

A minimal sample size of 1,000 completed participants with baseline and 12 month data will provide 90% power to detect small differences in primary outcomes effects at the 5% level of confidence for the whole group. Specifically, we will be able to detect:

• 5% weight loss

• increase of 2.5 g of fibre/1,000 kcal

• 3.4% reduction of fat intake as a percentage of total energy

• 2.7% reduction of saturated fat intake as a percentage of total fat intake

• 11.7 min/wk of increased physical activity.

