### Participants and recruitment

The Divisions of General Practice have recruited over 75 practices and 150 general practitioners (GPs) to participate in the study. This was done through expression of interest by letter and fax, information sessions and site visits. The main pre-requisite for inclusion was the practice having a computerised patient record system.

People aged 50-65 years (18 years and older in the indigenous subgroup) without known diabetes attending study general practices are approached to participate. A variety of methods are used to identify potential participants including opportunistic recruitment when the person attends the general practitioner for a routine consultation, using the practice's computer database to identify people in the target age range and sending a letter suggesting they attend for risk assessment, and local media advertising of the program.

Risk is assessed using the AUSDRISK tool, a questionnaire developed in Australia [16]. The questions focus on demographic and diabetes risk factors and include an objective assessment of waist circumference performed by trained research staff. The maximum AUSDRISK score is 38 and a score of ≥ 15 is considered high risk. A score of 15-19 is associated with a 1 in 7 chance and a score of ≥ 20 with a 1 in 3 chance of developing diabetes over the next 5 years [16]. A score of ≥ 12 is considered high risk in the indigenous subgroup.

A person with a risk score of ≥ 15 is required to undergo investigations to exclude prevalent diabetes. This initially involves measurement of capillary blood glucose in the general practitioner's surgery, followed by measurement of fasting plasma glucose and possibly an oral glucose tolerance test.

Study exclusion criteria include new or previously diagnosed diabetes, taking a hypoglycaemic medication in the past month, use of prescribed weight loss medication or a medical contraindication to participation in a physical activity program. Participants enter the study after written consent is obtained, eligibility criteria have been met and clearance is received from their general practitioner.

The study plans to recruit 1,550 high risk people into the lifestyle intervention program. Among these 100 will be Arabic-speaking, 100 will be Chinese-speaking and 100 will be indigenous people.

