### Intervention - Lifestyle Modification Program

The five aims of the lifestyle modifications are:

1. At least 30 min/day of moderate to vigorous intensity physical activity, including aerobic exercise 3 or more days/week plus strength training at least twice/week (210 min/week total structured exercise)

2. Reduction in the intake of energy from total fat to less than 30%

3. Reduction in the intake of energy from saturated fat to less than 10%

4. Fibre intake of at least 15 g/1000 kcal

5. Achievement of a 5% reduction in body weight at 12 months.

In addition to the 210 min/week structured exercise goal, participants are encouraged to increase incidental physical activity in ways which would enhance both cardiovascular and musculoskeletal fitness.

These five goals are entirely concordant with the Finnish DPS (5), which was one of the most successful diabetes prevention trials. The physical activity goal, which has been modified slightly from the Finnish DPS is based on a review of the physical activity prescriptions utilised in relation to outcomes achieved in all of the successful trials of diabetes prevention (5,6,7,10,11), considerations of cost and feasibility in this translational setting, as well as other literature regarding modality, volume, and intensity of exercise required to improve metabolic risk and body composition in similar cohorts. Both the Finnish DPS and the US DPP included resistance training (strength training) in their supervised exercise sessions and is explicitly specified within the physical activity goal of the SDPP. Resistance training is an anabolic form of exercise, differing substantially from aerobic exercise in its ability to induce muscle hypertrophy and associated metabolic and functional changes [17,18]. It improves insulin sensitivity, glucose homeostasis, blood pressure, dyslipidaemia, markers of inflammation and catabolism, and visceral obesity, thus addressing the key metabolic abnormalities in adults at high risk of type 2 diabetes [19,20]. Importantly, resistance training (but not aerobic exercise) attenuates or prevents the loss of lean tissue (muscle and bone) accompanying weight loss diets such as those prescribed in this study [21].

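### The goal-count primary outcome is taken at 12 months over the whole cohort, although up to four of the five goals can already be met at entry, so it mixes pre-existing behaviour with programme effect

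*Protocol article*

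**What the plan says.** The Intervention section of the protocol article sets five goals. Two are levels with no reference to a starting point: "At least 30 min/day of moderate to vigorous intensity physical activity" (210 minutes a week in total, with aerobic and strength components) and "Fibre intake of at least 15 g/1000 kcal". Two are worded as a fall to a level: "Reduction in the intake of energy from total fat to less than 30" per cent and "Reduction in the intake of energy from saturated fat to less than 10" per cent. The fifth, a 5% loss of body weight at 12 months, is a change from baseline.

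Under Participants and recruitment, entry depends on the diabetes risk score. The sentence that opens "Study exclusion criteria include new or previously diagnosed diabetes" goes on to certain medications and contraindication to physical activity. Neither the entry rule nor the exclusions refer to diet or activity at entry.

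Statistical methods places the analysis of goal achievement at 12 months and lists the "proportions of the cohort achieving 1,2,3,4, or all 5 goals" among the primary outcomes. It adds that "Logistic regression analysis will be used to examine factors associated with the achievement of program goals", with separate models for weight, activity and diet. It mentions neither attainment at baseline nor a comparison of attainment between the two time points. Impact Evaluation states that outcomes are assessed at baseline and at 12 months.

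**The concern.** For the goal count, the article fixes the denominator (the cohort), the time (12 months) and the label (achievement). Together these credit the programme with any threshold that a participant already met on entry and still meets. The study follows the active arm of earlier trials and has no comparator, so each participant's baseline is the only internal reference, and this outcome does not use it.

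Two results are at stake. The count could look substantial with no change in behaviour. And sub-groups that differ in diet or activity at entry, such as Divisions or men and women, could appear to respond differently to the programme when they only started from different places. The activity and diet models would carry the same mixture if baseline were left out of them.

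**Working it through.** **Inputs.** Four goals that may be met at entry and one that cannot (Intervention section). The whole cohort as denominator, at 12 months (Statistical methods). The article gives no baseline attainment rate, so every rate below is assumed. Its only numerical claim nearby is the power statement (1,000 completers, 90% power, 5% level). That concerns changes, and it cannot be reproduced because no standard deviation is given. Nothing here depends on it.

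**1. The goal count when nobody changes.** Let each threshold goal be met at entry with probability p. The weight goal then contributes nothing.

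- Independent goals: P(at least one) = 1 − (1 − p)^4. For p = 0.10: 1 − 0.90^4 = 0.344. For p = 0.25: 1 − 0.75^4 = 0.684.
- Complete overlap (the same people meet all four): P(at least one) = p, that is 0.10 to 0.25. No other pattern with these rates gives a smaller share.
- If the two fat goals are read as requiring a fall, only activity and fibre remain. Independent: 1 − 0.90^2 = 0.19 and 1 − 0.75^2 = 0.44. Complete overlap: again 0.10 to 0.25.

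The true change is zero in every line.

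**2. One goal with some movement both ways.** Let p0 be attainment at entry, r = 0.70 the share of those who keep the goal, and a = 0.10 the share of the others who newly reach it. Attainment at 12 months is p0·r + (1 − p0)·a.

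| At entry | At 12 months | Of achievers, already at goal | Net change |
|---|---|---|---|
| 10% | 0.07 + 0.09 = 16% | 0.07/0.16 = 44% | +6 points |
| 20% | 0.14 + 0.08 = 22% | 0.14/0.22 = 64% | +2 points |
| 30% | 0.21 + 0.07 = 28% | 0.21/0.28 = 75% | −2 points |
| 40% | 0.28 + 0.06 = 34% | 0.28/0.34 = 82% | −6 points |

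The 12-month proportion rises down the table while the net change goes from gain to loss.

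**3. What an attainment model would see without baseline.** Take the first and last rows as two sub-groups. They share the same r and a and differ only in p0. The odds ratio for attainment at 12 months is (0.34/0.66) / (0.16/0.84) = 0.515/0.190 = 2.7. It reflects the starting point alone.

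**The case against.** The strongest reply is that the evaluation is about change. The Abstract names changes in weight, activity and diet as the main outcomes, the impact evaluation is defined as change at 12 months, and the power targets are increases and reductions. With no change in behaviour these would sit near zero, and a reader would see it. That stands, and it limits the point to the goal count and the attainment models. It does not remove the point, because the count is itself listed as primary.

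Four stronger readings are tempting, and the article does not support them.

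- *The logistic models leave out baseline.* No covariate of any kind is named. Baseline is unnamed rather than excluded, and a fuller plan may include it.
- *Impact Evaluation judges attainment without baseline.* The sentence "Analyses of these data will determine whether the program goals are achieved by individuals, by the group as a whole" refers back to data from both time points, so it does not show this.
- *All four goals are plainly states.* The two fat goals are worded as reductions, and someone already below the level has, read literally, not reduced anything. Statistical methods carries no such rule into the count, so the definition is ambiguous. Activity and fibre have no such wording.
- *Inflated attainment enters the economic model.* Goal attainment is not named as an input in Economic Evaluation, and its examples of cost per outcome are changes, such as cost per kilogram lost.

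It is also fair to object that independence is implausible, since saturated fat is part of total fat. Positive dependence lowers the share meeting at least one goal, which is why the complete-overlap figure is given beside the independent one.

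**Conclusion.** The point holds for the goal count as stated. For the activity and diet attainment models it holds on the condition that they are fitted without the baseline value. It does not reach the continuous change outcomes, the power statement or the 5% weight goal.

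The size of the distortion cannot be derived from the article. The ranges above illustrate how large it could be under assumed entry rates of 10% to 25%; they do not estimate what this cohort will show. Even with complete overlap, the part credited without any change is not negligible. The count should be corrected before it is reported as a primary result, but the rest of the evaluation does not fall with it.

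**What to change.** For each of the four threshold goals, and for the count of those four, report the proportion at baseline, the proportion at 12 months, and the paired difference with a 95% CI. Add new attainment among participants not at goal on entry and, beside it, maintenance among those who were. The paired difference should lead. New attainment alone can arise from error in a three-day food record, without real change. State whether the two fat goals require a fall. The five-goal count can stay as a description of status at 12 months, with the weight goal shown separately as a change.

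In the activity and diet logistic models, include the baseline value of the outcome as a covariate, or restrict the models to participants not at goal on entry. The weight-loss model needs no change on this account.

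The cost is analysis wording only, because outcomes are already assessed at both time points. The downside is that reported achievement becomes smaller. Without a comparator, the paired difference is still a within-participant change and should be described as such.

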**Figure 1 F1:**
[figure not shown]
**Overview of the program and data collection points for evaluation**.

High risk individuals agreeing to participate in the lifestyle modification program complete an initial computer-assisted telephone interview (CATI) survey. This survey includes socio-economic and demographic information, physical activity habits, quality of life, and self-efficacy, as well as recent health service utilisation and current medication use. Participants are then scheduled to attend an individual consultation with a lifestyle officer. At this consultation, the lifestyle officers measure height, weight and waist circumference using calibrated stadiometers, scales and tape measures, following a standardized anthropometric protocol as specified by the International Society for the Advancement of Kinanthropometry (ISAK) [25]. The individual consultation includes a general discussion about diabetes risk and prevention, an overview of the program, and uses motivational interviewing techniques to assist participants to set goals and develop tools to self-monitor. Following this session, arrangements are made for participants to attend three two-hour group programs held over a six to eight week period. Lifestyle officers conduct these group sessions of approximately 10 people, which cover theoretical, behavioural and practical aspects of diet and physical activity. The overall program motto is: "Eat better and move more". Those who are not able to or do not want to attend a group program are offered the option of three individual health coaching sessions by telephone, covering the same material. The intervention delivered to indigenous participants will be slightly modified to take account of cultural issues.

Follow up telephone calls are made by the lifestyle officers to each participant at 3, 6 and 9 months to enquire about progress, assist with behaviour change and offer participants additional support as required.

In addition, participants are provided with details of local community-based lifestyle programs which have been evaluated by the research staff and found to be consistent with the goals of the SDPP. Participants have the option of enrolling in such programs as one way to assist in achieving the SDPP physical activity and dietary goals.

At 12 months the CATI survey is repeated and participants undergo an individual assessment with the lifestyle officer and their general practitioner.

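### Participants are nested in practices and intervention groups, but the predictor models and the power statement state no allowance for clustering

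*Protocol article*

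**What the plan says.** Under Statistical methods, the protocol article plans predictor analyses as follows: "Logistic regression analysis will be used to examine factors associated with the achievement of program goals". Separate models are planned for 5% weight loss, the activity goal and the dietary goals. On sample size, the same section states: "A minimal sample size of 1,000 completed participants with baseline and 12 month data will provide 90% power". That claim is made at a 5% level for the cohort as a whole. Five detectable changes are listed, such as "increase of 2.5 g of fibre/1,000 kcal" and an activity change of 11.7 min/week. The section gives no SD, formula, ICC or design effect, and no variance estimator for the models.

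The structure of the sample is described elsewhere. Setting names three Divisions of General Practice. Participants and recruitment says that these "have recruited over 75 practices and 150 general practitioners (GPs) to participate in the study" and sets a target of 1,550 recruits. The Intervention section, after Figure 1, says: "Lifestyle officers conduct these group sessions of approximately 10 people". It also offers individual telephone coaching to people who cannot or do not want to attend a group.

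Outcome measures and evaluation plan makes programme factors, as well as participant factors, a target of the predictor analysis. Impact Evaluation adds comparisons by Division and gender.

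**The concern.** People who share a practice, group sessions and a lifestyle officer are likely to change in similar ways. If the analysis ignores this, the standard error of a whole-group mean change is too small. So are the standard errors of predictors that differ mainly between clusters, such as practice, group, Division or programme features. The study means to inform policy on which features of such a programme work and in which settings, so the affected coefficients are among those that matter most. A nominal 5% test on them could reject too often. The same correlation lowers the effective sample size behind the power statement.

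**Working it through.** **Inputs from the article:** 1,000 completers; 90% power; 5% level (two-sided assumed, as sidedness is not stated); five detectable changes; over 75 practices; groups of about 10; 1,550 recruits.

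**Assumed:** ICC of 0.01 to 0.05, since the article gives none.

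**Step 1: can the 90% be reproduced?** Not directly, because no SD is given. Working backwards for a before-after mean change:

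- Detectable difference = SD × (1.96 + 1.2816)/√1,000 = 0.1025 × SD.
- Implied SD of change = stated difference/0.1025:

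| Outcome | Stated difference | Implied SD of change |
|---|---|---|
| Weight | 5% | 48.8 points |
| Fibre | 2.5 g/1,000 kcal | 24.4 g/1,000 kcal |
| Total fat | 3.4% | 33.2 points |
| Saturated fat | 2.7% | 26.3 points |
| Activity | 11.7 min/week | 114 min/week |

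The first four look far too large for their scales, so 1,000 was probably not the binding number for those outcomes.

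**Step 2: design effect.** DE = 1 + (m − 1) × ICC, and the interval widens by √DE.

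- Practices, m = 1,000/75 = 13.3: DE = 1.123 at ICC 0.01 and 1.617 at ICC 0.05. Widening is √1.123 = 1.06 to √1.617 = 1.27. Effective n is 890 to 619.
- Groups, m = 10: DE = 1.09 to 1.45. Widening is 1.04 to 1.20. Effective n is 917 to 690.

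Because over 75 practices were recruited, 13.3 is an upper bound on the mean practice size. Unequal practice sizes would push the design effect up.

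**Step 3: error rate of an unadjusted test.** For a whole-group mean change or a purely between-practice predictor, the true size of a nominal 5% test is 2 × (1 − Φ(1.96/√DE)). This is 6.4% at ICC 0.01 and 12.3% at ICC 0.05. It does not carry over to predictors that vary within practices.

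**Step 4: power if 90% is exact under independence.** Power = Φ(3.2415/√DE − 1.96).

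| ICC | By practice (m = 13.3) | By group (m = 10) |
|---|---|---|
| 0.01 | 86.4% | 87.4% |
| 0.02 | 82.7% | 84.7% |
| 0.05 | 72.2% | 76.8% |

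**Step 5: which outcomes does this touch?** With assumed SDs of 5 to 20 points (weight), 4 to 10 g/1,000 kcal (fibre), 6 to 10 points (fat) and 4 to 10 points (saturated fat), power stays at about 100% even at DE = 2.23, which is ICC 0.10 by practice. With a fat SD of 20 it is still 94.9%. For activity at SD 114, the table in Step 4 applies.

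**Step 6: does the larger recruitment target absorb the loss?** Suppose all 1,550 complete, so that m = 1,550/75 = 20.7. At ICC 0.05, DE = 1.983, effective n = 1,550/1.983 = 782, and power for activity = Φ(3.2415 × √0.782 − 1.96) = about 82%. At ICC 0.02, DE = 1.393, effective n = 1,113, and power is about 93%.

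**The case against.** The strongest objection is that this argues from silence. The article does not say that participants are treated as independent, and it does not exclude a robust variance or a random effect. A condensed article commonly leaves such detail to the full protocol or analysis plan. That stands to this extent: a reader might infer that the authors decided to ignore clustering, and the document does not show that. What remains is that the article fixes a model class and a sample size, states no allowance in either, and makes programme and Division factors explicit targets.

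A reader might also infer that power is overstated for every primary outcome. The documents do not support this. Without an SD and an ICC the 90% cannot be rebuilt, and the implied SDs suggest ample slack for weight, fibre, fat and saturated fat. For the same reason, inflating all five listed differences by 1.27 would be unsupported, since four of them do not look like true minimum detectable differences.

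Three further limits stand. The 1,000 is a minimum, and 1,550 are to be recruited. Group clustering does not apply to those coached individually by telephone, and the article does not say how many that will be. The number of lifestyle officers is not given, so no figure can be attached to clustering by officer. Finally, the power statement concerns whole-group change and not the logistic models, so the two parts of this point are related but separate.

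**Conclusion.** The point holds in a limited form. The nesting is documented and no allowance for it is stated. If the analysis is run as written and the ICC is positive, intervals for whole-group mean changes and for practice-, group- or programme-level predictors will be too narrow. The shortfall is a factor of about 1.06 to 1.27 for 13.3 completers per practice at an assumed ICC of 0.01 to 0.05. Predictors that vary within clusters, such as gender, may be little affected, and the direction of any error can differ.

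The effect on power is of practical interest only for the 11.7 min/week activity change. The fall to about 86-72% by practice or 87-77% by group rests on three assumptions: 90% is exact under independence, the test is two-sided, and the ICC lies between 0.01 and 0.05. The group figures also assume that everyone attends a group. Retention well above 1,000 would recover the activity power at the lower ICCs but not at 0.05.

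**What to change.** - Fit the goal-attainment and mean-change models as GEE or mixed models clustered on practice with robust variance, and include Division as a fixed effect. Name one of the two in advance, because their odds ratios have different meanings.
- Repeat the analysis with intervention group or lifestyle officer as the cluster, as a sensitivity analysis. Say how telephone participants are handled, for example as clusters of one in the group analysis.
- State the SD and the ICC assumed for each effect in the power statement.
- Restate power for the 11.7 min/week activity effect over a range of ICCs. Leave the other four listed differences unscaled until their SDs are stated.

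The cost is analysis wording and a short recalculation, with no new participants or visits, provided that practice, group and officer identifiers are kept in the participants' database. The price in the results is somewhat wider intervals and a less favourable power figure for activity.
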